## Abstract

**Background:**

Heart failure is a major cause of morbidity and mortality in society. Current medical therapy centres on neurohormonal modulation with angiotensin converting enzyme inhibitors and β-blockers. There is growing evidence for the use of metabolic manipulating agents as adjunctive therapy in patients with heart failure. We aim to determine the effect of perhexiline on cardiac energetics and alterations in substrate utilisation in patients with non-ischaemic dilated cardiomyopathy.

**Methods:**

A multi-centre, prospective, randomised double-blind, placebo-controlled trial of 50 subjects with non-ischaemic dilated cardiomyopathy recruited from University Hospital Birmingham NHS Foundation Trust and Cardiff and Vale NHS Trust. Baseline investigations include magnetic resonance spectroscopy to assess cardiac energetic status, echocardiography to assess left ventricular function and assessment of symptomatic status. Subjects are then randomised to receive 200 mg perhexiline maleate or placebo daily for 4 weeks with serum drug level monitoring. All baseline investigations will be repeated at the end of the treatment period. A subgroup of patients will undergo invasive investigations with right and left heart catheterisation to calculate respiratory quotient, and mechanical efficiency. The primary endpoint is an improvement in the phosphocreatine to adenosine triphosphate ratio at 4 weeks. Secondary end points are: i) respiratory quotient; ii) mechanical efficiency; iii) change in left ventricular (LV) function.

**Trial Registration:**

ClinicalTrials.gov: NCT00841139

ISRCTN: ISRCTN2887836

## Background

Despite recent advances in the treatment of heart failure (HF), it remains a condition with significant morbidity and mortality having a 5 year mortality rate that rivals most cancers[1]. In the developed world, heart failure affects 1-2% of the general population [2], causing about 5% of all adult hospital admissions, and complicating a further 10-15%[3]. Current pharmacological therapy centres on the management of symptoms with diuretics and neurohormonal modulation with angiotensin converting enzyme inhibitors and β-blockers. Energy deficiency plays an important role in the pathophysiology of HF and is held to be a promising target for HF therapy. Numerous studies support the finding of decreased cardiac energy levels and flux as a consistent feature of HF[4,5].

The main determinants of cardiac energetics and energy availability are substrate utilisation. The normal heart relies mainly on fatty acids for its energy requirements, accounting for up to 70% of the total energy requirement in the fasting state[6]. Glucose and other carbohydrates such as lactate make up much of the remainder. Mitochondrial phosphorylation represents the major route of energy generation. The heart is a metabolic omnivore and can adapt to utilise various substrates depending on requirements, but each substrate varies in its energy cost. Fatty acid oxidation (FAO) requires greater oxygen for a given quantity of adenosine triphosphate (ATP) synthesis than the use carbohydrates. In HF, there is typically a down regulation of fatty acid metabolism with preserved or increased glucose uptake, but often a relative block of entry of pyruvate in to the tricarboxylic acid cycle (TCA cycle).

These metabolic changes contribute to the energy starvation state found in heart failure of all aetiologies. Phosphorus-31 (P-31) magnetic resonance spectroscopy (MRS) is used to non-invasively estimate ATP and phosphocreatine concentration and the PCr/ATP ratio. Phosphocreatine is an important short-tem energy store that maintains a high phosphorylation potential under conditions of rapid increased energy demand such as exercise. ATP levels are maintained at steady concentration to maintain energy for muscle contraction and normal cellular function. The myocardial PCr/ATP ratios is reduced in HF and correlates with New York Heart Association (NYHA) class[5].

Perhexline maleate is a metabolic modulating agent that gained popularity in the 1970's as an antianginal therapy until it was linked to both peripheral neuropathy [7] and hepatotoxicity[8]. It has since been shown that the risk of toxicity can be dramatically reduced by maintaining plasma concentrations in an established normal range of between 0.15 and 0.6 mg/L[9]. In the isolated rat heart, perhexiline acts, at least in part, by shifting myocardial substrate utilisation from fatty acids to carbohydrates through the inhibition of carnitine palmitoyltransferase-1 (CPT-1) and, to a lesser extent, carnitine palmitoyltransferase-2 (CPT-2). These mitochondrial enzymes act to facilitate the entry of medium and long chain fatty acids into the myocytes as their main energy source. Their inhibition causes a reciprocal increase in glucose and lactate utilisation and thus an improvement in myocardial efficiency and energy status by forcing the omnivorous myocytes to metabolise carbohydrate and reduce the net oxygen consumption.

A growing body of studies support the use of P-31 MRS to measure this improvement in myocardial energetics as a response to treatment. Fragasso et al [10] have demonstrated an increase in cardiac PCr/ATP ratio with the metabolic modulating agent trimetazidine in subjects with heart failure. Our group has recently shown an improvement in cardiac energetics using perhexiline in patients with hypertrophic cardiomyopathy[11].

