### Randomisation and Drug Monitoring

Following baseline investigations ensuring normal liver function tests, participants will be randomised by computer to commence with perhexiline 200 mg oral daily or an identical placebo for one month (Figure 1). Randomisation will be done in a 50:50 ratio of perhexiline:placebo in blocks of 10.

At one week duration, all patients will have a blood sample taken for serum perhexiline level with the researcher blinded to the subject's treatment allocation. This level will be evaluated by a doctor unblinded to the subject's treatment allocation. The dosage of perhexiline will be adjusted according to the accepted dosing protocol (Table 2). An equal number of dummy dose adjustments will be made to those patients on placebo to help to maintain blinding.

**Table 2 T2:** Perhexiline dose titration according to serum perhexiline level.

*Perhexiline concentration (mg/L)*	*Recommended new daily dose (mg)*
0.00-0.05	300
0.05-0.15	250
0.15-1.00	200
1.00-1.50	100
1.50-2.00	50
>2.00	Cease for 1 week and start 50 mg alternate days

At the end of one month of therapy, patients will undergo a repeat of baseline investigations and a further perhexiline level will be taken to ensure therapeutic levels were achieved and compliance maintained.

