### Monitoring and Safety Assessments

When perhexiline levels are unmonitored, it has been associated with both hepatotoxicity and peripheral neuropathy. All patients will be screened both clinically and biochemically for any sign of these conditions. Perhexiline also lowers serum glucose levels. Patients who are diabetic will be made aware that the medication may cause hypoglycaemic and they will be instructed make frequent blood sugar measurements when starting the study. Perhexiline levels will be tested at one week and at the end of the study as outlined above.

All adverse events, including serious adverse events (SAEs), will be recorded and followed up for the duration of the study or until resolution. Assessment of adverse events will be performed by study investigators. All SAEs will be graded and reported to the sponsor. Any suspected unexpected serious adverse reactions will be reported to the sponsor, ethics committee and the Medicines and Healthcare Products Regulatory Agency. This study has been reviewed and approved by the South Birmingham Research Ethics Committee. Written informed consent will be obtained from all study participants.

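### Table 2 makes no dose reduction until the week-1 level exceeds 1.00 mg/L, although the Background ties reduced toxicity to an upper limit of 0.6 mg/L

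*Protocol article*

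**What the plan says.** Three parts of the protocol article bear on this.

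- **Background.** The early toxicity problems, peripheral neuropathy and hepatotoxicity, are said to be largely avoidable by "maintaining plasma concentrations in an established normal range of between 0.15 and 0.6 mg/L". No other target or safe range appears anywhere in the article.
- **Randomisation and Drug Monitoring.** On the starting dose: "participants will be randomised by computer to commence with perhexiline 200 mg oral daily or an identical placebo for one month". A sample is taken at one week and read by an unblinded doctor, and then: "The dosage of perhexiline will be adjusted according to the accepted dosing protocol (Table 2"). Table 2 gives 300 mg up to 0.05 mg/L, 250 mg up to 0.15, 200 mg from 0.15 to 1.00, 100 mg up to 1.50, 50 mg up to 2.00, and above that a one-week stop followed by 50 mg every other day. Placebo subjects are covered too: "An equal number of dummy dose adjustments will be made to those patients on placebo to help to maintain blinding". At the end of the month, "a further perhexiline level will be taken to ensure therapeutic levels were achieved and compliance maintained".
- **Monitoring and Safety Assessments.** "When perhexiline levels are unmonitored, it has been associated with both hepatotoxicity and peripheral neuropathy". The same section confirms that there are two levels in all: "Perhexiline levels will be tested at one week and at the end of the study as outlined above". It adds a general safeguard: "All patients will be screened both clinically and biochemically for any sign of these conditions".

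**The concern.** The Background gives concentration control as the reason perhexiline can be used with acceptable safety, and it gives the limits of that control. Table 2 is the only rule in the article that turns a measured concentration into a dose. It acts on the lower limit exactly, since the dose rises below 0.15 mg/L. It does not act on the upper limit, since nothing changes at 0.6 mg/L and the first reduction comes only above 1.00 mg/L. The two statements therefore agree on the side that protects efficacy and disagree on the side that protects against toxicity.

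The table is unambiguous and will be followed. A subject with a week-1 level of, say, 0.8 mg/L would stay on 200 mg, outside the only range the article offers, with the rule obeyed to the letter. What is at stake is the safety margin for subjects on perhexiline. The sample size, the randomisation and the comparison of PCr/ATP do not depend on it.

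**Working it through.** **Inputs**

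- Stated range: 0.15 to 0.6 mg/L (Background).
- Band with no dose change: 0.15 to 1.00 mg/L, 200 mg daily (Table 2).
- First reduction: 1.00 to 1.50 mg/L, 100 mg daily (Table 2).
- Levels: one at week 1, one at the end (Randomisation and Drug Monitoring; Monitoring and Safety Assessments).
- Treatment: 4 weeks, taken as 28 days. Subjects: 50, randomised 1:1.

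**Step 1. Compare the limits.**
- Lower: 0.15 against 0.15, no difference.
- Upper: 1.00 / 0.60 = 1.67, and 1.00 − 0.60 = 0.40 mg/L.
- Share of the no-change band that lies above the stated range: 0.40 / (1.00 − 0.15) = 0.40 / 0.85 = 47%. This is a share of the band's width, not of subjects.

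The Background speaks of plasma and the monitoring section of serum, but both use mg/L. A level of exactly 1.00 mg/L falls in two adjoining rows, which does not alter the comparison.

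**Step 2. Size of the dose response.**
- From 0.6 to 1.00 mg/L: (200 − 200) / 200 = 0% reduction.
- Just above 1.00 mg/L: (200 − 100) / 200 = 50% reduction.

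**Step 3. Can a later level correct the dose?** Two levels are planned. The second is taken once therapy is complete and serves to confirm exposure and compliance. So 1 of 2 levels can change the dose, and the week-1 decision governs (28 − 7) / 28 = 21 / 28 = 75% of treatment.

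**Step 4. Would a level above 0.6 mg/L come back into range unaided?** All active subjects start on 200 mg and no loading dose is described. Assume stable clearance and adherence. If the level is still building up at week 1, it would be expected to rise on the same dose. If it has reached its plateau, it would be expected to stay where it is. In neither case would it be expected to fall below 0.6 mg/L.

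**Step 5. How many subjects?** The article gives no distribution of week-1 levels, so the number cannot be derived. The only bound is the size of the active arm: 50 / 2 = 25.

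**The case against.** The strongest reply is that the two figures do different jobs. The Background describes a range for maintained concentrations, taken from a cited source. Table 2 is a one-off titration rule for an early level and is described as an accepted scheme. A maintenance range and an early action limit need not share an upper bound, and the shared 0.15 suggests a link without proving one. This is possible, but the article does not say it. Nor does the distinction remove the problem: with no loading dose described, an early level already above the range gives no reason to expect a later level inside it.

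A second reply is that subjects are otherwise protected. Liver disease, existing neuropathy and interacting CYP2D6 inhibitors are exclusions. Liver function is checked before randomisation and again at one month. Screening and adverse-event follow-up are planned, and treatment lasts only four weeks. All of this stands and limits the expected harm. None of it controls the concentration itself.

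Two stronger readings are tempting and should be resisted.

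- A reader might infer that Table 2 is wrong or unsafe. The article does not support that. It calls 0.15 to 0.6 mg/L a normal range in which risk is much lower and does not call 0.6 a toxicity threshold. It links toxicity to unmonitored levels, whereas levels here are monitored. It gives no risk figure for 0.6 to 1.00 mg/L. The factor of 1.67 is a ratio of cut-offs, not of exposure or risk.
- A reader might infer that 150 mg is the correct dose for the gap, because it is the only 50 mg step missing between 300 and 50 mg. That is a pattern in the table, not pharmacology, and the last row breaks the pattern anyway.

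**Conclusion.** The point holds as an unexplained conflict between the article's stated safe range and its dosing rule, and it bears on patient safety. The upper limits differ by 0.40 mg/L (a factor of 1.67) while the lower limits agree, and no later planned level can change the dose during the 21 days after the week-1 sample. These statements follow directly from the text. The expectation that a level above 0.6 mg/L stays there or rises rests on stable clearance and adherence, and on no loading dose being given.

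Which limit is right cannot be settled from the article, because it depends on the cited source for the range and on the source dosing protocol. Harm at 0.6 to 1.00 mg/L over four weeks is not shown. The number of subjects affected is unknown and is at most about 25. Power, randomisation and the primary PCr/ATP analysis are unaffected. The conflict should be resolved before subjects are dosed, because the titrating doctor will follow the table as printed.

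**What to change.** First, the clinical team confirms the upper limit against the source dosing protocol. The next step depends on the answer.

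- **If 0.6 mg/L holds:** end the 200 mg band at 0.6 mg/L and add one row for levels above 0.6 and up to 1.00 mg/L with a reduced dose. The clinical team sets that dose. One example is 150 mg, a cut of (200 − 150) / 200 = 25%, which lies between the present 200 and 100 mg steps. Match each change with a dummy change on placebo through the process already planned.
- **If 1.00 mg/L is the right week-1 action limit:** leave Table 2 alone, and either correct the Background figure or add a sentence saying why the week-1 limit differs from the maintenance range.

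The second route costs one sentence. The first costs one table row, a few extra dose changes with their matching dummy changes, and somewhat lower exposure in the subjects concerned. Neither needs an extra visit or blood sample, and neither changes the sample size or the primary analysis.

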## Methods

### Hypothesis

Treatment with perhexiline increases cardiac PCr/ATP ratio, increases cardiac respiratory quotient (indicating relatively greater carbohydrate utilisation), and improves LV mechanical efficiency and left ventricular function in patients with dilated cardiomyopathy.

### Study Design

This is a multicentre prospective, randomised, double-blind, placebo-controlled trial of 50 subjects with dilated cardiomyopathy (defined as an ejection fraction (EF) <40% in the absence of evidence of coronary artery disease) who are stable on conventional heart failure therapy. Inclusion and exclusion criteria are detailed in Table 1.

**Table 1 T1:** Inclusion and exclusion criteria.

*Inclusion Criteria*
Non-ischaemic, dilated cardiomyopathy
Symptomatic despite optimally-tolerated medical therapy
Impaired left ventricular systolic function (LVEF < 40%) as assessed by resting echocardiography
*Exclusion Criteria*
History of liver disease or liver function test measurements greater than twice the upper normal limit
Concomitant use of amiodarone, quinidine, haloperidol or selective serotonin re-uptake inhibitors that inhibit the CYP2D6 enzyme
Pre-existing evidence of peripheral neuropathy
Women of child bearing potential
Patients with any contraindication to magnetic resonance imaging such as an implantable cardiac device or claustrophobia
Obesity (BMI > 35)
Obstructive sleep apnoea

### Baseline Studies

All patients will undergo a baseline visit (see flowchart - Figure 1) during which the following will be performed; i) detailed review of past medical history, drug history and tobacco and alcohol consumption; ii) clinical examination of all systems; iii) assessment of NYHA class from history; iv) completion of a Minnesota Living with Heart Failure (MLWHF) questionnaire; v) measurement of height and weight; vi) 12-lead electrocardiogram (ECG); vii) office brachial blood pressure and heart rate measurement following 15 minutes rest; viii) collection of fasting serum and plasma for haematological and biochemical analysis including glucose and liver function tests; ix) storage of serum and plasma at -80°c for future assay of biomarkers of heart failure such as pro-terminal brain natriuretic peptide (BNP); x) transthoracic echocardiography to determine left ventricular size and function; xi) cardiac magnetic resonance spectroscopy to determine the cardiac PCr/ATP ratio;

**Figure 1 F1:**
[figure not shown]
**Summary of study timeline**. Following baseline investigations, 50 patients will be randomised to recieve 200 mg of perhexiline or matched placebo for one month. At one month all baseline tests will be repeated and a subgroup will undergo cardiac catheterisation.

Baseline tests will be repeated in full after completing one month of treatment with perhexiline or placebo. A willing subgroup of patients will undergo right and left heart catheterisation for invasive haemodynamic measurements and cross heart sampling. Those subjects taking part in the invasive subgroup will also undergo cardiac magnetic resonance imaging (CMR) for accurate estimation of left ventricular cardiac mass.

Female subjects of child-bearing potential will be excluded from the study.

### Cardiac Magnetic Resonance Spectroscopy

Cardiac high-energy phosphate metabolism will be measured using P-31 MRS on a 3-Tesla Philips (Philips Healthcare, Reigate, Surrey) Achieva whole-body magnet using a linearly polarized transmit and receive P-31 coil with a diameter of 14 cm. Localization will be achieved by image selected in-vivo spectroscopy (ISIS) volume selection. The participants will be positioned supine with the coil directly over the precordium. The coil will be secured in place by straps around the upper body and coil. The participants will then be positioned inside the magnet with the center of the coil at the isocenter of the magnet. Survey images will be obtained to check the position of the coil. The subjects and/or the coil will be repositioned if required to ensure that the distance between coil and septum and apex of the heart is minimized and maximize signal strength. Localized iterative 1^st ^order shimming will be performed including the entire heart using the unsuppressed water signal acquired with the body coil as reference. The shimming process involves an automated Hydrogen-1 spectral acquisition to test the quality of the shim that is expressed as a full width at half maximum (FWHM). This is repeated until a FWHM of less than 40 Hz is achieved. A short axis cine scan will be acquired to calculate the trigger delay for ECG triggering and to check quality of shimming and F_0 _determination. The trigger delay will be calculated such that the spectra is acquired in the diastolic period when the heart is a still as possible. The 3-dimensional ISIS voxel of acquisition will be planned to include most of the septum and apex of the heart within the shimmed area. Care will be taken to minimize blood contamination from the right ventricle, liver and skeletal muscle as much as possible. The voxel size will be kept constant at 89.54 ml (44 × 55 × 37 mm^3^) to allow comparisons between different subjects and scans. Following this the P-31 spectrum will be acquired with a repetition time of 10000 ms and 512 averages. A repetition time of 10000 ms has found to be optimal for adequate reduction of saturation effects without increasing the scan time greatly. The total scan time will be 23 minutes. The spectra will be analyzed and quantified on the java based Magnetic Resonance User Interface (jMRUI) software. Post-processing will be performed with 15 Hz Gaussian line broadening and Fourier transformation. Phase correction will be performed with PCr peak as the reference peak. Quantification will be performed with AMARES (Advanced Method for Accurate, Robust and Efficient Spectral fitting), time domain fitting program, which involves selecting peaks and defining their line width[12]. The concentrations of PCr, ATP (γ, α and β) and 2,3-diphosphoglycerate (2,3-DPG) will then be calculated as the area under the peaks. PCr/ATP ratio will be determined after correcting the γ ATP peak for blood contamination as described previously based on the quantity of 2,3-DPG in the derived spectrum[13]. A single, blinded operator experienced in the technique will perform analysis.

### Cardiac Magnetic Resonance Imaging

Cardiac magnetic resonance imaging will be performed on the same 3 Tesla Philips Achieva system using a cardiac coil with patients in the supine position. Serial contiguous short axis cines will be piloted from the vertical long axis and horizontal long axis images using standard manufacturer supplied sequences. Analysis will be performed offline (Philips ViewForum Ver 4.1) by a single blinded observer for the assessment of ventricular volumes, ejection fraction and left ventricular mass.

### Echocardiography

A standard transthoracic echocardiogram (Vivid 7, GE Vingmed Ultrasound, Horten, Norway) will be performed with the subject in the left lateral decubitus position by a single experienced echocardiographer using second harmonic imaging and an M3S multi-frequency transducer. All parameters will be measured in triplicate and averaged as per the recommendations of the American Society of Echocardiography[14]. Analysis will be performed offline by a single blinded observer using an EchoPAC workstation (GE Vingmed Ultrasound, Horten, Norway). Ventricular dimensions, wall thickness, chamber volume, stroke volume and ejection fraction will be determined by standard methods[15]. Resting left ventricular diastolic function will be determined using standard techniques[16]. Peak systolic (S'), early diastolic (E') and late diastolic (A') mitral annular velocities will be measured at end expiration at the septal, lateral, inferior and anterior left ventricular walls with real time pulsed wave tissue Doppler[17].

Greyscale images for 2-dimensional left ventricular strain will be acquired in cine-loop format in triplicate from the apical 4-, 2- and 3-chamber views and parasternal short axis views at basal, papillary and apical ventricular levels at end expiration at frame rates >70 Hz for offline analysis using commercially available software (Speqle Tracking, GE Healthcare, United Kingdom). The endocardial border will be manually tracked at end-systole and the software generates a region of interest over the myocardium. This enables frame-to-frame tracking of ultrasonic speckles that change position according to surrounding tissue motion throughout the length of the cardiac cycle. Peak systolic velocities, strain, strain rate, rotation and twist will be measured for each myocardial segment in triplicate and averaged.

